## Background

Delirium is associated with increased morbidity and mortality, cognitive impairment, dementia, and higher institutionalization rates [1]. The incidence of postoperative delirium (POD) depends on factors predisposing to delirium such as age, the presence of brain damage, dementia, deficits in cognitive, sensory, or mobility functions, multiple comorbidities, polypharmacy, and frailty [2]. Early indicators of cognitive deficits, including hyposmia [3], sleep disorders [4, 5], and subjective memory impairment [6, 7], are also relevant risk factors for delirium. The perioperative phase is a major trigger of postoperative delirium because of the administration of anesthesia, the surgical procedures, and other factors related to the operation itself, such as pain and immunological activation [2]. Postoperative cognitive dysfunction (POCD) often appears after POD [8, 9] and has been studied in relation to the preoperative status in order to measure the delirium’s impact, particularly on the risk of developing dementia [10], and in order to estimate the related health costs. POD and POCD are associated with higher mortality and postoperative complications (such as infections, falls, decubitus ulcers, incontinence) [9], with prolonged hospital stays [11], with the need for longer/extended intensive care and therapy and higher nursing workload burden [12], and with increased costs for both hospitals and healthcare insurance providers [2, 13].

Delirium is a healthcare quality indicator in older adults, and therefore delirium prevention is an essential parameter for patients’ safety [14, 15]. The incidence of delirium and its severity and duration can be significantly decreased and may be stratified by taking delirium risk factors into account [16]. Current guidelines for POD management [17] emphasize the importance of delirium prevention. A multimodal nonpharmacological approach [14, 18] is considered the best pathway [16, 19]. In a meta-analysis [20], this approach reduced the delirium risk by 53% (95% CI, 0.38 to 0.58) when comparing intervention and control groups.

For elective surgery, it is possible to implement a preadmission delirium prevention plan [21], adapting care to the patient’s age and delirium risk. However, surgical centers typically do not implement preadmission procedures for delirium risk assessment, and recommended interventions for the management of delirium are not standardized.

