#### Intervention

The intervention implements a cross-sectoral all-encompassing multimodal delirium prevention and management approach, and will be carried out in each study center after the center is randomized to take part in the intervention phase of the trial:All personnel training: within 4–6 weeks before the start of the intervention phase, nurses and therapeutic, medical, and support staff involved in the care of study patients will be trained with respect to dementia and delirium care, delirium diagnosis, and depression using a standardized training plan. Staff will be trained to three different levels of expertise: more than 70% of the staff are to receive basic training (90-min training time); more than 20% of nurses are to receive advanced training (“delirium scout” training—450-min training time); and more than 10% are to receive expert-level training (“delirium champion” training—900-min training time). Additionally, at least 70% of the physicians will receive 90 min extra of specific training about delirium risk, diagnosis, treatment, and prevention. The courses will be adjusted to the specific surgical and anesthesiological departments and special care units in order to ensure comparable levels of knowledge between different study sites.Environmental orientation support: the hospital environment will be adapted to the special needs of the patients. The decline of sensory function in older adults often leads to additional psychosocial stress, and is exacerbated by cognitive impairment. To address these issues, appropriate posters and signage will be placed on the wards, and in patients’ rooms and restrooms. Tools for temporal and situational orientation will be made available; for example, whiteboards with personal information, date, season, and year, as well as analog clocks that can be seen from the bed. Moreover, appropriate tools to prevent falls will be provided, such as anti-sliding socks. Special boxes for glasses, hearing aids, and dentures, as well as sleeping masks and ear plugs will be within reach of the patients at all times.Preadmission phase: the trained staff will implement some nonpharmacological preventive interventions in this phase, including informative talks and written recommendations for patients, and instructive contacts with the referring doctors regarding the age-appropriateness of prescribed medications and interventions.“Best practice” multimodal intervention: participants at the respective centers will receive perioperative and postoperative multimodal delirium prevention and care management between 8 a.m. and 8 p.m. on 7 days of the week, modified according to best practice models such as the Hospital Elder Life Program (HELP) [26], “The old patient in the surgery room” [22], or the Care of Confused Hospitalised Older Persons (CHOPs) [27]. Psychogeriatric nurses and one physician who have received 900 additional minutes of “delirium champion” training will form a multiprofessional consultation–liaison-like intervention team that will contact the patients and address their special needs daily. They will facilitate the implementation of the treatments advised in international delirium prevention guidelines [17, 23]: adaptation of surgery and anesthesia, medication and pain treatment appropriate for the patients’ age, pain monitoring, avoidance of movement restrictions such as catheters or infusions, and avoidance of benzodiazepines and anticholinergic drugs. These specialists will prescribe meaningful individualized daily activities for preventing delirium, defined in six modules: reorientation, cognitive activation, mobilization, meal companionship, clinical diagnostics and operation room attendance, and nonpharmacological sleep promotion and anxiety reduction. A team of nurses’ aides or volunteers (mostly gap-year social work volunteers) will carry out these activities, as well as chaperone patients during the diagnostic procedures, and in the operating and recovery rooms. They will receive 40 h of theoretical and practical training on the modules, and will be available daily in two shifts of 12 h per day.Patients and their family members will be advised individually about delirium risk and prevention, and will receive information materials (leaflets, posters, etc.) about delirium and the care service. Moreover, family members will provide individual information about the patient, facilitating individualized care and communication, and will be advised to support some individualized delirium prevention activities.

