#### Timelines

The study started in November 2017, and the recruitment phase will last until April 2019.

There will be three follow-up examinations after 2, 6, and 12 months, with the last planned for April 2020. We plan to complete the evaluations and cost analyses by December 2020.

From the patient’s perspective, the study will start with a preadmission screening (T0, at most 3 weeks before admission) (see Fig. 3). Admission (T1) will be followed by surgery and then daily delirium screening for 7 days (T2–T8) during hospitalization. A final discharge assessment (T9) will take place 1–8 days after surgery. If, at this point, the patient is considered to suffer from delirium, then delirium screening and monitoring will continue for another 2 weeks, so long as the patient remains hospitalized in the center. The discharge examination (T9) will take place, at the latest, 3 weeks after the elective surgery, with the participation of a physician who will note any postoperative complications. Follow-up assessments will be performed after 2 months (T10), 6 months (T11), and 12 months (T12). Moreover, the patient’s relatives will be asked at T12 about their care burden using the G-ZBI, and the cognitive state of the patient will be assessed using the IQCODE instrument. If a patient is unable or unwilling to go to the regional center for any follow-up assessment, the local PAWEL team will offer the assessment either at some hospital closer to the patient or at the patient’s general physician’s practice. If the patient is not able to go to any of these places, a team member will assess the patient at the patient’s home. Finally, if the patient refuses this option, he or she will be asked for a telephone interview.

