#### Statistical analysis

For the primary outcome, logistic regression analyses with cluster adjustment are planned.

For the secondary outcomes, the changes in the medication and the care burden of the patients’ relatives, we plan analyses using mixed linear and logistic regression models, with fixed and random factors for estimating heterogeneity over clusters [68].

Subgroup analyses for specific patient groups (e.g., patients with cardiac surgery regarding cognitive status or patients with brief hospital stays/brief surgeries) are planned.

For planned validity assessments of postoperative delirium, the validity of the I-CAM-S and NuDESC vs the RASS will be evaluated as screening tools for postoperative delirium. Diagnostic test performance of the tools will be evaluated by receiver operating characteristics (ROC) analysis.

Missing data (due to nonadherence of a department or a particular patient) will be documented. We will apply mixed-effect models, which handle the missing data without using any imputation method. Mixed-effect models assume that the missing data are missing at random (MAR); that is, when the probability that an outcome is missing is related to some other fully observable variable in the model, but not to the variable with the missing value itself [69].

Regarding the health-economic evaluation, a micro-costing analysis will be carried out using data from the clinical administration of two hospitals (Tübingen and Stuttgart). Moreover, for the patients insured by a specific health insurance (AOK Baden-Württemberg) who consent, the health and care insurance costs of the 12 months before and after surgery will be calculated using a difference-in-difference approach [70]. In this case, the target parameter is the cost per avoided POCD. The cost-effectiveness of the intervention will be calculated comparing the costs of the intervention group and the control group. In addition, quality-adjusted life years (QALYs) will then be calculated using data from the EQ-5D-5 L form about health-related quality of life, and applied for calculating the incremental cost-effectiveness. When possible, subgroup analyses will be carried out, for example, by age or gender, to determine whether cost-effectiveness is different in the corresponding groups. Sensitivity analyses will also be performed. The evaluation will be carried out following the recommendations of the “Good practice secondary data analysis” (GPS).

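### The planned brief-stay/brief-surgery subgroup is not tied to planned values; if actual stay is used, intervention-control comparisons within it are open to bias

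*Protocol article*

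**What the plan says.** The Statistical analysis section of the protocol article plans subgroup analyses and names two examples. One is cardiac surgery in relation to cognitive status; the other is "patients with brief hospital stays/brief surgeries) are planned". It gives no cut-off and does not say whether stay and duration are planned or actual. The Inclusion criteria, by contrast, speak of a planned duration of surgery of at least 60 minutes.

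Four other statements bear on this:

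- Background: postoperative delirium and cognitive dysfunction are associated "with prolonged hospital stays".
- Intervention, before admission: "the trained staff will implement some nonpharmacological preventive interventions in this phase".
- Intervention, during the stay: "participants at the respective centers will receive perioperative and postoperative multimodal delirium prevention and care management". The team's tasks include "adaptation of surgery and anesthesia".
- Timelines: surgery is followed by "daily delirium screening for 7 days (T2–T8) during hospitalization", and the discharge assessment falls 1 to 8 days after surgery.

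**The concern.** A subgroup supports a comparison of intervention with control only if membership does not depend on which of the two a patient received. Actual length of stay does not meet that condition. It is settled after prevention has started, it is linked to the primary outcome, and it is fixed while that outcome is still being recorded. Brief-stay patients in the intervention phase and brief-stay patients in the control phase may then be different kinds of patients.

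Actual surgery duration has a milder form of the problem, because adapting surgery and anesthesia is part of the intervention.

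At stake is the answer for short-stay surgery. The Dissemination policy section aims at a care pathway for routine use. A spurious lack of benefit, or apparent harm, in short-stay patients could misdirect that pathway.

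**Working it through.** **Inputs from the protocol.** The Sample size section assumes delirium in 25% of control and 15% of intervention patients. The ratio is 0.15/0.25 = 0.60, which agrees with the reduction of at least 40% aimed for in the Design section. The overall odds ratio is (0.15/0.85)/(0.25/0.75) = 0.53. The protocol gives no figure for this subgroup, so there is none to reproduce.

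**Assumed inputs.** The protocol does not give the probability of a brief stay. Write b_d for that probability in delirious patients and b_n in non-delirious patients. For the illustration, b_n = 0.50 and b_d = 0.15 under control.

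**Formula.** With delirium risk p, P(delirium | brief) = p·b_d / [p·b_d + (1−p)·b_n]. For long stay, replace each b by 1−b. It follows that the brief-stay odds ratio equals the overall odds ratio × (b_d intervention / b_d control) ÷ (b_n intervention / b_n control).

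**Case A: the intervention raises b_d to 0.25 and leaves b_n at 0.50.**

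- No true effect (25% in both phases), brief stay: control 0.0375/0.4125 = 9.1%, intervention 0.0625/0.4375 = 14.3%, risk ratio 1.57.
- No true effect, long stay: control 0.2125/0.5875 = 36.2%, intervention 0.1875/0.5625 = 33.3%, risk ratio 0.92.
- True effect (25% to 15%), brief stay: intervention 0.0375/0.4625 = 8.1%, risk ratio 0.89.
- True effect, long stay: intervention 0.1125/0.5375 = 20.9%, risk ratio 0.58.

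**Case B: stay changes only through delirium (b_d = 0.15 and b_n = 0.50 in both phases).**

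- No true effect: the ratio is 1.00 in both strata.
- True effect, brief stay: 9.1% against 0.0225/0.4475 = 5.0%, risk ratio 0.55, odds ratio 0.53.
- True effect, long stay: 36.2% against 0.1275/0.5525 = 23.1%, risk ratio 0.64, odds ratio 0.53.
- The odds ratio is undistorted, but the brief-stay risk difference is not −10 points. If delirious patients are half as likely to have a brief stay, the rates are 14.3% and 8.1% (−6.2 points). If a quarter as likely, they are 7.7% and 4.2% (−3.5 points).

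**Case C: other direct effects on stay, no true effect on delirium.**

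- Both probabilities rise in proportion (0.50 to 0.60, 0.15 to 0.18): brief-stay risk ratio 1.00, long-stay 40.6%/36.2% = 1.12.
- Only b_n rises (0.50 to 0.60, b_d stays at 0.15): brief stay 0.0375/0.4875 = 7.7% against 9.1%, risk ratio 0.85. A null effect now looks like benefit.

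**Simulation.** One million patients were simulated. All of the following is assumed: stay = 9 days + 1.5 days per SD of frailty + 0, 2 or 4 days for delirium − 0, 1 or 2 days direct intervention effect + normal error with SD 2 days; brief means 8 days or less; the log odds ratio of frailty for delirium is 1.

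| Scenario | Brief-stay OR, no true effect | Brief-stay OR, 25% to 15% |
|---|---|---|
| No direct effect on stay | 1.00 | 0.48–0.50 |
| Direct effect 1–2 days, delirium adds 0 days | 1.17–1.34 | 0.59–0.68 |
| Direct effect 1–2 days, delirium adds 2 days | 1.52–2.24 | 0.74–1.12 |
| Direct effect 1–2 days, delirium adds 4 days | 2.04–4.04 | 1.02–1.91 |

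In the last row delirium among brief-stay patients is only about 1 to 2% or less, so those ratios rest on very few events. For comparison, the effect in patients who would be brief-stay under control is an odds ratio of about 0.51–0.52 in the scenarios with a direct effect. A subgroup fixed at baseline (low frailty) gives 1.00 under the null and 0.48–0.49 under the effect in every scenario.

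**The case against.** The strongest reply is that the phrase is an example in parentheses, that subgroup definitions are commonly left to an analysis plan not shown here, and that planned stay may be what was meant. This stands in part: the protocol does not rule out planned values. But the text does not say planned, although the Inclusion criteria do say it for surgery duration. The issue is also not a missing cut-off, since no cut-off on actual stay removes the problem.

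A reader might infer more than the documents support:

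- *That the subgroup estimates are biased.* This needs a direct effect of the intervention on stay, which the protocol does not state. Without one, the odds ratio is undistorted in Case B and nearly so in the simulation, and the planned primary model is logistic.
- *That longer stay is a consequence of delirium.* The Background reports an association.
- *That stay is known only after the outcome window.* The discharge assessment falls on days 1 to 8 and screening runs for 7 days, so stay is set largely within the window.
- *That delirium is the outcome analysed.* The sentence names none for this subgroup. For cognitive outcomes at later visits, stay is still set after the intervention begins, but the ratios above do not carry over.
- *That fewer in-hospital I-CAM ratings in brief-stay patients are part of this defect.* Any short-stay group has fewer, including one defined by planned stay, so the fix does not cure it. A chart review at discharge supplements the ratings.

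**Conclusion.** The point holds as a poorly chosen, or at least unsafely worded, subgroup variable. Comparisons within actual brief stay are open to bias, and within actual brief surgery to a lesser degree. The distortion ranges from none on the odds-ratio scale, if stay changes only through delirium, to a null effect that appears as a brief-stay risk ratio of 1.57 (apparent harm) or 0.85 (apparent benefit) under the assumed stay probabilities. The absolute effect in brief-stay patients shrinks even without a direct effect on stay. All magnitudes use the protocol's 25% and 15% but rest on assumed stay probabilities and, for the distorted ratios, on an assumed direct effect. This is a supporting analysis; the primary comparison, the sample size and the conduct of the trial are untouched.

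**What to change.** State in the analysis wording that the subgroup is defined by variables fixed before the intervention can act: planned procedure or specialty, and planned cut-to-suture time. Test it with an intervention-by-subgroup interaction in the planned regression model. Label any analysis by actual stay or actual duration as descriptive, with no claim about the intervention effect.

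The cost is small. It is a short change of wording, with no change to design or recruitment. Planned duration is an eligibility criterion, but the protocol does not say that the value itself is recorded. If only eligibility was recorded, the value must be captured. The protocol mentions no expected stay per procedure, so planned categories will only approximate actual stay.

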In this study, we will develop a cross-sectoral and “best practice” multimodal delirium prevention approach in five medical centers. The proposed multisectoral model for delirium prevention integrates and builds upon several multimodal admission models [16] with preadmission risk reduction counseling (“prehabilitation”), perioperative monitoring [22], and training based on international guides [17, 23] of multidisciplinary patient care providers, including operation room personnel, service staff, and families. The study will optimize delirium assessment, establish a cross-sectoral intervention bundle for preventing delirium, and evaluate the effectiveness and cost-efficiency of this all-encompassing approach. To this end, evidence-based delirium diagnoses, neuropsychological tests, and multimodal multiprofessional interventions will be implemented. Follow-up POCD evaluations will be performed 2, 6, and 12 months after surgery. Furthermore, relatives will be asked about their care burden, and a cross-sectoral analysis of the perioperative patient pathway will be performed.

The project, recruiting a total of 1500 patients, has the following objectives:The evaluation of the perioperative delirium prevalence with the I-Confusion Assessment Method-based scoring system for delirium diagnosis and delirium severity (I-CAM-S) [9], which is used for the first time in a large multicenter German sample.The implementation of a multisector, individualized, multiprofessional and multimodal delirium and POCD prevention program.The evaluation of the prevalence of POCD at 2 and 6 months after surgery, and the persistence of POCD after 12 months.The evaluation of changes in medication during the pre-admission and perioperative phases, especially with respect to avoidance of anticholinergic drugs and other pharmacologic agents associated with delirium.The evaluation of the care burden of the patients’ relatives.The economic evaluation of the multimodal intervention, studying its cost-effectiveness. From the point of view of the hospital departments, initial hospital costs will be evaluated. From the point of view of the health and care insurance company Allgemeine Ortskrankenkasse (AOK) Baden-Württemberg (Germany), inpatient and outpatient costs during the 12 months before and after the surgery will be analyzed in relation to outcome differences.

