**Fig. 3 Fig3:**
[figure not shown]
Standard Protocol Items: Recommendations for Interventional Trials figure of enrollment, intervention, and assessments. CSHA Clinical Frailty Scale of the Canadian Study of Health and Aging, EQ-5D-5L EuroQol five dimensions questionnaire, G-ZBI German Zarit Burden interview, I-CAM-S I-Confusion Assessment Method-based scoring system for delirium severity, IQCODE Informant Questionnaire on Cognitive Decline in the Elderly, MNA-SF Mini Nutritional Assessment Short Form, MoCA Montreal-Cognitive Assessment, NOSGER II Nurses’ Observation Scale for Geriatric Patients, NRS Pain Numerical Rating Scale of Pain, NuDESC Nursing Delirium Screening Scale, PHQ-4 Patient Health Questionnaire, PSQI (Basic) Pittsburgh Sleep Quality Index (Basic), RASS Richmond Agitation–Sedation Scale, SF-12 12-Item Short Form Survey, SMI subjective memory impairment, TMT Trail Making Test, V1/V2/V3 parallel versions of the MoCA, STOP BANG Sleep Apnea Questionnaire (snoring, tiredness, observed apnea, blood presure, body mass index, age, neck circunference, gender)

For *planned validity assessment of postoperative delirium*, the validity of the I-CAM-S and NuDESC vs the Richmond Agitation-Sedation Scale (RASS) [66] and vs chart review will be evaluated. The RASS is a simple observational scale that quantifies the level of consciousness, assessing both sedation and agitation.

For *analysis of delirium severity*, the duration and extent of restraints and one-to-one supervision requirements will be used, in addition to the CAM-S score.

For *process analysis*, acceptance and feasibility will be evaluated by qualitative assessment using focus groups formed by members of the geriatric centers.

For *planned health-economic analyses*, the initial hospital costs and the costs per delirium of two centers (Tübingen and Stuttgart) will be assessed. Moreover, for the patients whose health insurance is AOK Baden-Württemberg (Germany), health and care insurance expenditures and utilization will be assessed, in particular regarding hospital care, outpatient care, medication, rehabilitation, and nursing care. For a precise evaluation of the costs, the expense for training and staff carrying out the intervention will be included in the analyses.

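### The insurer-cost difference-in-difference splits time at surgery, but the intervention starts in the preadmission phase, so any insurer cost it causes before surgery is subtracted as baseline

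*Protocol article*

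**What the plan says.** The cost windows are stated twice in the protocol article. The objectives in the Background say that "inpatient and outpatient costs during the 12 months before and after the surgery will be analyzed in relation to outcome differences". The Statistical analysis section adds the estimator: "the health and care insurance costs of the 12 months before and after surgery will be calculated using a difference-in-difference approach". It names the cost per avoided POCD as the target parameter of this analysis.

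The Intervention section lists a preadmission phase as one component and says that "the trained staff will implement some nonpharmacological preventive interventions in this phase". These include talks and written advice for patients, and "instructive contacts with the referring doctors regarding the age-appropriateness of prescribed medications and interventions". The Background objectives include evaluating "changes in medication during the pre-admission and perioperative phases".

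The Timelines section has the patient's course begin with "preadmission screening (T0, at most 3 weeks before admission" and then says "Admission (T1) will be followed by surgery". The paragraph on planned health-economic analyses, after Fig. 3, describes the insurer costs as "in particular regarding hospital care, outpatient care, medication, rehabilitation, and nursing care". It also says that training and staff expense for the intervention will be included.

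Nothing in the article sets an index date other than surgery for these costs, or takes the preadmission phase out of the baseline.

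**The concern.** A difference-in-difference uses the before period to remove differences between groups that the intervention did not cause. That requires a before period which the intervention has not touched. Here the before period runs up to surgery, while the part of the intervention that crosses sectors acts earlier and is aimed partly at outpatient prescribing. Medication and outpatient care are among the costs counted.

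A cost change caused before surgery is therefore not just lost. It sits in the term that is subtracted, so it enters with the opposite sign. An added outpatient cost would make the intervention look cheaper, and a saving on drugs would make it look dearer. The Design section aims to show that better quality of life comes at no additional cost, so a bias in the cost difference bears on a stated aim.

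**Working it through.** The plan gives no cost figure to reproduce, so the check is algebraic.

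**Inputs from the protocol article**
- Split at surgery, 12 months on each side, difference-in-difference (Background objectives; Statistical analysis).
- Intervention content before admission (Intervention).
- T0 at most 3 weeks, or 21 days, before admission, with surgery after admission (Timelines).
- POCD effect: a fall from 20% to 10% (Sample size), or a reduction of at least 20% (Design). Read as relative and applied to 20%, the latter is 0.20 × 20% = 4 points.

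**Estimator.** Let a be the insurer cost per patient caused by the intervention before surgery, and b the cost caused after it. Write P for the background cost before surgery and F for that after it, with subscripts I and C for the groups, and let the usual parallel-trend condition hold: F_I − P_I = F_C − P_C.
- Stated rule: [(F_I + b) − (P_I + a)] − [F_C − P_C] = b − a.
- Full incremental cost: a + b.
- Error: (b − a) − (a + b) = −2a.

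**Illustration.** The values of a and b are assumed, in EUR per patient, with b = −500 throughout.

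| a | Stated rule (b − a) | Full cost (a + b) | Error |
|---|---|---|---|
| +200 | −700 | −300 | −400 |
| +100 | −600 | −400 | −200 |
| +50 | −550 | −450 | −100 |
| 0 | −500 | −500 | 0 |
| −50 | −450 | −550 | +100 |
| −100 | −400 | −600 | +200 |

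**Per avoided POCD.** The numerator error is divided by the risk difference: −2a/0.10 = −20a at 10 points and −2a/0.04 = −50a at 4 points.

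**Share of the baseline exposed.** 21/365 = 5.8%. If 7 further days before surgery are assumed, 28/365 = 7.7%.

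**When the total changes sign.** The product (b − a)(b + a) = b² − a² is negative only when a is larger than b in absolute value. Take instead a constant daily effect r that starts 21 days before surgery and lasts 365 days after it, so that a = 21r and b = 365r. The rule gives 365r − 21r = 344r against a true 365r + 21r = 386r. The error is −42r = −2 × 21r, an attenuation of 42/386 = 10.9% with the sign kept.

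**With the split moved.** If the baseline ends before the preadmission phase and follow-up starts there, a falls in follow-up. The rule then gives a + b, with error 0 under the same parallel-trend condition.

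**The case against.** The strongest reply is that this is a small matter in a condensed article. The health-economic plan is one paragraph, the full plan may define the estimator and index date more closely, and sensitivity analyses are promised. The preadmission content is mainly talk and advice by study staff, whose expense the article includes separately. What remains is the downstream change in claims over a few weeks, while most of the intervention comes later. Windows anchored at surgery are also equal in length and easy to standardise.

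Most of this limits the size of the error and does not defend the split. The windows are stated outright in two places, so they are not a detail left open, and the promised sensitivity analyses are not specified. Training and staff expense is indeed unaffected if it is added outside the claims data; the article does not say to which period it is assigned.

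A reader might infer four stronger things that the article does not support.
- That the preoperative days of the index stay are counted as baseline. The text does not say how that stay is assigned.
- That the whole cost result is reversed. Only the part caused before surgery changes sign, and a lasting medication effect would be attenuated.
- That the error favours the intervention. This holds only if a is positive, and less prescribing could make it negative.
- That the cost per QALY carries the same error. The article does not say that this ratio uses the difference-in-difference figure.

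**Conclusion.** The point holds in a limited form. The stated baseline includes time in which the intervention is already acting, and the rule estimates b − a where a + b is wanted. The error of −2a per patient lies in the numerator of the cost per avoided POCD, and more patients would not remove it.

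Its size and direction cannot be derived from the documents; every euro amount above is an assumption. At most about 5.8% of the baseline is exposed, plus any days between admission and surgery, so the error is probably small. That bound reads the Intervention and Timelines sections together: the 3-week limit is given for T0 screening, and the preadmission contacts themselves are not dated. The point concerns one economic analysis in consenting patients of one insurer and does not touch the delirium or POCD comparisons.

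**What to change.** In the Background objectives and the Statistical analysis section, define the cost windows as follows for both groups:
- **Baseline:** 12 months ending at a uniform date before the preadmission phase, for example 3 weeks before admission. If preadmission contacts can occur earlier than T0, the date must precede them.
- **Follow-up:** from that date to 12 months after surgery, with the whole index stay included.
- **Sensitivity analysis:** the split at surgery, as now written.

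State also that training and staff expense is added outside the claims data.

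The cost is a few sentences of wording and a claims request that reaches back about 3 weeks further, with no new data from patients. The drawback is that follow-up becomes slightly longer than baseline, by 21 days plus any days between admission and surgery. The rule is the same in both groups, so background cost in the extra days cancels as far as the groups' daily background costs agree.
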